### 2.9. Sample Size Calculation

The sample size is based on an estimate using data from two previous simulation studies [35,49]. Ventilation is expected to be provided for 8 min only (given the time necessary to prepare ventilation devices). In an adult scenario lasting 10 min, there were 39 ventilations in the IAM group (with a target rate of 10/minute) and 19 in the BVM group [35]. In this study, targeting a ventilation rate of 20–30/minute, around 100 ventilations are expected in the IAM group. In the BVM group, 40 ventilations are to be expected if a ratio of 15 compressions to 2 ventilations is applied. The tidal volume should be similar in both groups, around 52 mL worth 25 mL of alveolar ventilation. The expected difference in alveolar minute ventilation between basic airway management and IAM devices is 185 mL (125 mL versus 310 mL). The standard deviation is estimated to be 140 mL [49]. To be conservative, the correlation used to compute the calculation is 0. With an alpha set at 5% and a power of 90%, 15 teams (30 simulations) are required. Given the harmless study design (simulation), more groups will be accepted if available.

### 2.10. Blinding, Bias Minimization, and Data Collection and Extraction

To prevent assessment bias, data will be gathered automatically through the manikin’s sensors, and extracted to a comma-separated values (CSV) file. Variables of interest will be generated using a custom-coded PHP script. Demographics and consent will be collected using an electronic form hosted on a Joomla 4.2 website (Open-Source Matters, New York, NY, USA). Missing data will be treated as such. No imputation technique will be used. The curated dataset will be sent in DTA file format to the data analyst, who will be blinded as to group allocation (all data that could potentially lift the blinding will be removed). The “.dta” file format is a proprietary binary format designed to be used with Stata data analysis software. All investigators will have full access to the curated data file. 

### 2.11. Statistical Analysis

Data distribution will be assessed graphically, and when in doubt, using the Shapiro-Wilk test. The variables will be described accordingly using either means (standard deviations and/or 95% confidence intervals) or medians (quartiles). 

The dependency of the variables, due to the crossover design, will be taken into account either using paired tests (paired Student’s *t*-test, Wilcoxon matched-pairs signed-rank test or sign test depending on the assumptions) or by applying non-paired tests on the difference (Student’s *t*-test, or Wilcoxon–Mann–Whitney test). Analyses will be performed on an intention-to-treat basis.

A two-sided *p*-value lower than 0.05 will be considered significant. The data will be analyzed using Stata V15.1 (StataCorp-LLC, College Station, TX, USA).

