### 2.5. Study Groups, Second Randomization and Concealment of Allocation

The second level of randomization will take place immediately after the self-managed training session. The teams will be randomized to one of the two study paths by opening an opaque, sealed envelope conceived using a block randomization list generated online by [name] ([name]) using a 1:1 ratio, with block sizes of 2 and 4 and stratification according to the trial centers [48]. This stratification will be used to account for differences in the approaches of the participants (e.g., initial airway management strategy, task distribution, local procedures during CPR, quality processes or prior specific training). 

The AHA guidelines will be considered as standard approach [49]. These guidelines recommend alternating 15 compressions and 2 ventilations, starting with compressions [9].

The experimental approach consists in the immediate insertion of an i-gel^®^ device with no prior ventilation. Chest compressions are delivered continuously once the cardiac arrest has been identified. Once i-gel^®^ has been inserted, ventilations should be performed at a rate of 20 to 30 per minute, as recommended by the AHA [9].

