The scenario will start with a clinical description to expose the life-threatening condition of the patient. One of the investigators will state: *“Here is Cayla, a 9-month-old child who was left unattended for 10 min. She was found cyanotic by her parent who called the emergency call center. A few minutes later, she collapsed. She is now unconscious, limp, cyanotic, and apneic. A medical mobile unit has already been dispatched and will be on site in about ten minutes.”* A rephrasing will be asked of the team leader to ensure correct understanding (closed-loop communication). The team leader will then pick up the top envelope of the stack, and open it to discover the path to follow, starting either with the standard or experimental approach. The simulated child will be apneic and pulseless if checked. After placing the pads, asystole will be displayed on the defibrillator’s screen. CPR waves will be automatically shown when compressions are delivered to increase the fidelity of the simulation. Regardless of the treatment given, all subsequent rhythm analyses will show refractory asystole. Participants will be able to successfully obtain intraosseous/intravenous access on their first attempt. There will be no further intervention or educational follow-up after the study period. Team members will be asked to alternate their position after every 2 min cycle. At the end of the scenario (T0 + 10 min), participants will be shown a normal sinus rhythm, and ROSC will be present. All the equipment will be fully restored. Then, the same scenario will be played a second time using the other airway management strategy, with no more interactions between the study team and the participants nor between the participants. 

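### The crossover analysis lets paired tests with no period term stand in for period-adjusted tests, with no rule for choosing between them

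*Protocol article*

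**What the plan says.** Section 2.11 names only the within-team dependency. It offers two families of test: paired (t, signed-rank, sign) and unpaired on a difference (t, Wilcoxon-Mann-Whitney), joined by a plain alternative: "Wilcoxon matched-pairs signed-rank test or sign test depending on the assumptions) or by applying non-paired tests on the difference". The clause on assumptions governs the choice among the paired tests. Nothing governs the choice between the families, and neither is named for the primary outcome. Period, sequence, order and learning are not mentioned.

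Three other sections bear on this:

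- Section 2.7 has each team do two scenarios back to back: "Then, the same scenario will be played a second time using the other airway management strategy".
- Section 2.5 randomises teams to sequence "using a 1:1 ratio, with block sizes of 2 and 4 and stratification according to the trial centers".
- Section 2.9 concludes: "With an alpha set at 5% and a power of 90%, 15 teams (30 simulations) are required". It also accepts further teams if available.

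**The concern.** The two families do not answer the question in the same way. A paired test of experimental minus standard leaves any difference between first and second scenario inside the data. An unpaired comparison of period differences between the two sequences removes it.

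The design gives period effects an opening. In the second scenario the team already knows the case, the rhythm, that vascular access will succeed and when the parent will speak. Learning could improve performance, and a second 10-minute resuscitation could bring fatigue. Times to first compression and to epinephrine, and the chest compression fraction, look at least as exposed as the primary outcome.

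At stake are the width of the confidence intervals, the true size of the test and, when sequences are unequal, the position of the estimate. An analyst following the text could also choose an adjusted or an unadjusted answer after seeing the data.

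**Working it through.** **Inputs from the documents.** Section 2.9 gives a difference of 185 mL in alveolar minute ventilation (125 versus 310), 90% power and the following: "The standard deviation is estimated to be 140 mL" and "To be conservative, the correlation used to compute the calculation is 0". Section 2.11 gives the two-sided 5% level.

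**The plan's own figure.** The SD of the within-team difference is 140 × √(2 × (1 − 0)) = 198 mL. A paired t-test with the noncentral t distribution has power 0.898 at 14 teams and 0.919 at 15. So 15 is the smallest number reaching 90%, and the stated sample size is reproduced. It assumes no period effect.

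**Model.** Let τ be the treatment effect and π the shift from first to second scenario. A team's experimental-minus-standard difference has mean τ + π if the experimental approach comes second (n1 teams) and τ − π if it comes first (n2 teams), with N = n1 + n2. The documents do not give π, so 70 mL (half an SD) and 140 mL (one SD) are assumptions.

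**Shift of the paired estimate** = π × (n1 − n2)/N.

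| Split | π = 70 mL | π = 140 mL |
|---|---|---|
| 8:7 | 70 × 1/15 = 4.7 mL | 9.3 mL |
| 9:6 | 70 × 3/15 = 14 mL | 28 mL |
| 10:5 | 70 × 5/15 = 23 mL | 47 mL |

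Against 185 mL, the π = 70 mL column is 2.5%, 7.6% and 12.6%.

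**Error variance of the paired test.** The expected squared SE is [198² + π² × 4·n1·n2/(N(N − 1))]/N. With π = 140 at 8:7, 4 × 8 × 7/(15 × 14) = 1.067, so it is (39,200 + 19,600 × 1.067)/15 = 4,007 and the SE is 63.3 mL. The real sampling SE of the paired mean is √(39,200/15) = 51.1 mL. The reported SE is therefore 63.3/51.1 = 1.24 times too large.

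**Simulated operating characteristics, 8:7 split, correlation 0.**

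| Assumed π | Type I error, paired | Power for 185 mL, paired | Power for 185 mL, adjusted |
|---|---|---|---|
| 0 | 4.9% | 92% | 91.5% |
| 70 mL | 3.9% | 91% | 91.5% |
| 140 mL | about 2% | 86% | 91.5% |

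The adjusted test holds about 5% type I error throughout. At 9:6 the paired test also stays below 5%. At 10:5 with π = 140 mL it rises to just under 7%.

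**Period-adjusted analysis.** The estimate is the mean of the two sequence means, so π cancels. Its SE is ½ × 198 × √(1/n1 + 1/n2) with N − 2 = 13 degrees of freedom: 51.2, 52.2 and 54.2 mL at 8:7, 9:6 and 10:5. Power for 185 mL is 91.5%, 90.6% and 88.3%.

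**How unequal the sequences could be.** The number of centres is not given. With 15 teams and blocks of 2 and 4, one centre always gives 8:7. Three centres of five give 8:7 in 75% of draws and 9:6 in 25%. Five centres of three give 8:7 in 63%, 9:6 in 31% and 10:5 in 6%.

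**Which difference.** The unpaired option works only on first-minus-second differences. The same unpaired test on experimental-minus-standard differences compares τ + π with τ − π, and so tests the period effect, not the treatment. Section 2.11 does not say which difference is meant.

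**The case against.** The strongest reply is that the right test may already be listed. Unpaired tests on the difference, applied to period differences by sequence, are the standard period-adjusted analysis, and a separate analysis plan may settle the choice. This stands in part: a suitable method is not absent. But the published text presents the paired tests as an equal alternative, so following it to the letter can give an unadjusted result.

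A second reply is that the period effect may be small for the primary outcome. Ventilation depends largely on the assigned strategy, training precedes both scenarios and no feedback is given. That is fair. The size is unknown, and every figure above that uses it is conditional.

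Three stronger readings are tempting, and the documents do not support them:

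- A reader might infer that the treatment estimate is biased as a matter of course. The shift is zero with equal sequences, one fifteenth of the period effect at 8:7, and averages to zero over the 1:1 randomisation.
- A reader might infer that false positives are inflated. Among the splits examined this happens only at 10:5, which centre-stratified small blocks make uncommon. Otherwise the paired test is conservative.
- A reader might infer that listing the sign test breaks the 90% power claim, since its power at 15 teams would be 74%. That figure assumes normal differences, where the sign test would not be chosen, and an attained level of only 3.5%.

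**Conclusion.** The point holds as a should-fix. Section 2.11 treats as interchangeable two analyses that differ in whether they remove period, in a design where a period effect is plausible and 15 teams cannot split equally. At near-equal splits the main consequence is a conservative test and intervals that are too wide: with an assumed period effect of a full SD at 8:7 and correlation 0, type I error is about 2% and power for 185 mL about 86% instead of 91.5%. With a more modest 70 mL the power loss is negligible. The shift in the estimate is a second, conditional consequence, modest unless the split is well off balance.

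A reader might go further and infer that the primary conclusion is at risk or that the sample size is wrong. Neither follows. If the true effect is near 185 mL, the conclusion is unlikely to reverse, and any positive within-team correlation raises power further: at an assumed 0.5, the paired test keeps about 98% power even with a 140 mL period effect at 8:7. The figures rest on an assumed period effect, normal differences, no differential carry-over and the plan's own SD.

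**What to change.** In section 2.11, name one primary analysis: the unpaired t-test comparing within-team period differences (first minus second scenario) between the two sequences, halved to give the treatment effect with its 95% confidence interval. The equivalent mixed model, with treatment and period fixed and team random, would serve as well. Name Wilcoxon-Mann-Whitney on the same period differences as the only fallback, and state when it applies. Remove the paired t, signed-rank and sign tests as primary options.

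In section 2.10, state that coded period and sequence stay in the dataset sent to the blinded analyst. Otherwise the removal of potentially unblinding data could make the adjustment impossible.

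The cost is wording and one degree of freedom. With 15 teams, power for 185 mL is about 91.5% at 8:7, 90.5% at 9:6 and 88% at 10:5, compared with 91.9% for the paired test when there is no period effect. Only the 10:5 split falls below the 90% target, and the planned number of teams need not change.

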### 2.12. Confidentiality

Study participants’ information will be kept confidential. Data regarding study participants will be coded. No identifying information will be revealed or transferred to third parties.

### 2.13. Criteria for Discontinuing or Modifying Interventions

Each team will be allocated two 30 min slots. The first slot will consist in the self-managed training session. The second slot should enable participants to complete the two 10 min scenarios.

There will be no interim analysis since the study will take place over a limited period and because no harm could result from simulation-based CPR scenarios.

## 3. Results

### 3.1. Milestones

The findings will be presented at scientific congresses and submitted for publication in a peer-reviewed, international journal, regardless of the results. It should be submitted in the first half of 2023. 

### 3.2. Protocol Version

The current version of this protocol is 1.0 (5 December 2022). Study sessions are expected to take place in January and February 2023. All protocol modifications will be clearly detailed in the final manuscript.

### 3.3. Trial Registration

This study is registered at https://clinicaltrials.gov/ (accessed on 10 August 2022) under the trial registration number NCT05498402.

### 3.4. Data Curation and Availability

The curated database will be deposited on Yareta [55] and will be immediately available before the final manuscript will be submitted for peer review. The original documents and files will be safely stored.

## 4. Discussion

The possibilities of addressing some of the knowledge gaps identified by the International Liaison Committee on Resuscitation (ILCOR) through clinical studies are particularly limited when the pediatric population is involved [56]. In this context, simulation-based studies could provide significant data. The protocol outlined in this manuscript could provide useful evidence and help to determine the most appropriate airway management strategy.

The main limitation of this study is that it will be conducted on a manikin. Therefore, there will be no direct evidence regarding actual clinical outcomes. Nevertheless, should different airway management strategies lead to different ventilation parameters, the same should be true in real clinical situations. However, the successful insertion rates could differ between simulated and actual OHCAs. 

In this trial, pediatric OHCA scenarios will be managed by two providers only. Actual clinical outcomes might prove different depending on the presence of BLS-trained bystanders, of prehospital physicians, or of other prehospital providers. The presence of trained rescuers can indeed enable the team leader to assign tasks, such as high-quality chest compressions, to these additional providers, thus allowing the ambulance crew to concentrate on other aspects of CPR management (such as airway management, crisis resource management, parent inclusion, rhythm analyses and ALS treatments). This could impact CPR quality because of fatigue, organizational aspects and differences in cognitive load, thereby limiting the generalization of the results gathered during this study. 

Another limitation is that the manikin could prove to be more difficult to ventilate with i-gel^®^ devices than actual patients. Indeed, airtightness improves over time when i-gel^®^ devices are used [57]. This is due to the thermoplastic properties of the non-inflatable cuff, which forms a progressively more efficient seal around the larynx after warming to body temperature. A field trial could, therefore, be considered according to the results that will be gathered during this study. 

While technical issues such as computer failure or manikin breakdown could prevent us from gathering the complete data (unavoidable attrition), quality control checks will be performed prior to each study session to limit the occurrence of such issues.

The strengths of this protocol are the use of the SPIRIT guidelines, the randomized crossover design, the specific and little-explored outcomes studied and the multicenter design. By comparing two airway management strategies, this study could help to address an evidence gap regarding the optimal airway management strategy in the case of pediatric OHCA. Its results could support the external validity and implementation of the most efficient airway management strategy in current practice.

## 5. Conclusions

This study could help to ascertain whether early IAM using an i-gel^®^ device improves the ventilation parameters in a pediatric simulated model of OHCA. The results generated by this trial could help to determine the most appropriate airway management strategy in this uncommon, yet critical situation.

## Figures and Tables

**Figure 1 children-10-00148-f001:**
[figure not shown]
Study flowchart.

**Figure 2 children-10-00148-f002:**
[figure not shown]
Study sequence.

**Table 1 children-10-00148-t001:** Trial schedule.

	Study Period			
	Enrolment	Intervention		Close-Out
Timepoint	*t* _0_	*t* _1_	*t* _2_	
**STUDY PROCEDURES**				
Recruitment and consent	✓			
Eligibility check	✓			
Teams of two	✓			
30 min self-managed training	✓			
**ASSESSMENTS**				
Participants’ characteristics	✓			
Randomization	✓			
Standard approach		[figure not shown]		✓
Experimental approach				✓
✓: Performed				

## Data Availability

Not applicable.
